### Allocation and randomization

A 4-size permuted block randomization is used. The randomization is computer-generated, in particular the allocation to the intervention or the control group is concealed and performed by the randomization module of the Research Electronic Data Capture system (REDCap) before the start of the exercise program, ensuring blinding of the research team [16, 17]. The sequence of randomization is decided by the patient’s record identifier in REDCap, which is received after signing informed consent. An open label study is performed, which means that the therapist/assessor and patients are not masked for the allocation to the intervention or control group. The therapist giving the exercise program and the assessor are the same individual during the entire study period.

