### Trial design

A parallel, two-arm, open label trial will be conducted. This single center prospective randomized clinical study will be performed to investigate the effectiveness and the feasibility of a comprehensive supervised exercise program (CSEP) in addition to usual supportive care compared to usual supportive care alone in patients undergoing CRT for HNC, the EffEx-HN trial. This is a superiority trial design because we aim to investigate whether a CSEP is more effective in improving health-related quality of life than the current standard of supportive care. To study the feasibility of the CSEP, a qualitative study will be performed in a subgroup of participants of the large prospective randomized clinical study described above. Quantitative data on feasibility will be collected in all participants.

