### Eligibility criteria

HNC patients are eligible to participate if they are scheduled for radiotherapy at the Radiation-Oncology department of the University Hospitals Leuven. Inclusion criteria are as follows: (1) ≥ 18 years, (2) diagnosed with primary malignant tumor head and neck region, (3) ECOG performance score 0–1, (4) able to complete baseline assessments prior to start of (chemo)radiotherapy, (5) physically and mentally capable of taking part in an exercise program and motivated to engage in a supervised exercise program. Patients are excluded if one of the following exclusion criteria are present: (1) < 18 years, (2) ECOG performance score ≥ 2, (3) treated with palliative intent, (4) evidence of distant metastases, (5) no basic level of reading and writing in Dutch. Participation of a patient in the study can be discontinued based on the participant’s request or if the disease is worsening, to the extent that exclusion criteria are present (treatment with palliative intent, evidence of distant metastases).

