### Sample size

The study was powered to have at least 80% power to detect based on a two-sided test with alpha equal to 0.05 a difference of 10 points in general health-related quality of life measured with the EORTC QLQ-C30 (primary outcome) between both groups at the primary endpoint, i.e., 6 months post-diagnosis. A drop-out of 5%, 10%, and 20% is anticipated at 6 weeks, 12 weeks, and 6 months, respectively. Based on reference values for the EORTC QLQ-C30, a standard deviation of 22.7 was assumed [49]. Further, moderate correlations equal to 0.5 were assumed for the associations with the baseline measurement. Under these assumptions, 75 subjects per group are necessary. The study was also powered on one key-secondary outcome, i.e., the physical functioning subscale of the EORTC QLQ-C30. Since the assumed standard deviation for this subscale was slightly lower (based on the EORTC QLQ-C30 reference values 2008), this has no impact on the required sample size. Otherwise said, with 75 subjects per group, the power is higher than 80% for this secondary outcome, more specific 87.7%.

For the feasibility study, no sample size calculation was performed.

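### One fixed, published block size of 4 in an open-label, single-centre trial could let anyone counting past allocations deduce about a third of them, which weakens REDCap concealment without removing it

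*Protocol article*

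**What the plan says.** All references are to the Protocol article.

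- **Block size.** Allocation and randomization: "A 4-size permuted block randomization is used". No second size and no random variation in size is described.
- **Concealment.** The same section says that "the allocation to the intervention or the control group is concealed and performed by the randomization module" of REDCap, and closes that sentence with "ensuring blinding of the research team". A patient's place in the sequence follows the REDCap record identifier, which is issued once consent has been signed.
- **Masking.** Still in that section, "the therapist/assessor and patients are not masked for the allocation to the intervention or control group". One individual is both therapist and assessor throughout. The CSEP section adds that the therapist coordinates the project.
- **Centre and strata.** Trial design: "This single center prospective randomized clinical study will be performed". No stratification factor is named anywhere.
- **Entry.** Eligibility criteria require patients to be judged physically and mentally capable of exercise and "motivated to engage in a supervised exercise program". According to Participant screening, recruitment, and consent, the principal investigator and a member of the research team speak to eligible patients before consent.
- **Numbers and timing.** Sample size: "Under these assumptions, 75 subjects per group are necessary". Trial status puts the end of recruitment at about the end of 2024.

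**The concern.** A central system such as REDCap conceals the list. It cannot conceal an allocation that follows logically from a known block size and the allocations already made. Both ingredients are available here: the block size is in print, and past allocations are visible because the trial is open label at one site.

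Foreknowledge does harm only if someone can act on it. The opening is at approach and screening, where motivation and capability are matters of judgement, and in the timing of consent, which decides which slot a patient takes. Both traits plausibly relate to adherence and to self-reported quality of life, the primary outcome. The planned constrained longitudinal analysis adjusts for baseline quality of life. At the assumed correlation of 0.5, however, baseline accounts for only 0.5² = 25% of outcome variance, so adjustment would correct only part of any selective entry.

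Separately, the claim that the research team is blinded sits badly beside the statement that the therapist/assessor is not masked.

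**Working it through.** **Inputs.** Block size 4 (Allocation and randomization). Seventy-five per group, so N = 150 (Sample size). The 1:1 ratio is inferred from the equal groups; it is not stated in words. One list is assumed, since one centre is stated and no strata are named.

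**The plan's own figure.** The plan gives no predictability figure. The only stated figure used here is 75 per group, and it reproduces closely:
- Baseline-adjusted SD = 22.7 × √(1 − 0.5²) = 19.66.
- n = 2 × [19.66 × (1.960 + 0.842) / 10]² = 60.7 per group.
- Allowing for 20% dropout, 60.7 / 0.8 = 75.8, or 77 if n is first rounded up to 61.
- With 75 × 0.8 = 60 completers per group, power is 79.6%. The use of earlier visits in the longitudinal model plausibly covers the small gap. The sample size is not in question.

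**Allocations that can be deduced with certainty.** A 2:2 block of 4 has 6 equally likely orders.
- First and second: never certain.
- Third: certain when the first two match, probability 1/3.
- Fourth: always certain.
- Share = (0 + 0 + 1/3 + 1) / 4 = 1/3 = 33.3%.
- 150 patients make 37 full blocks plus 2 patients: 37 × 4/3 = 49.3 allocations, and 49.3 / 150 = 32.9%.

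**Best-guess success**, always naming the arm that is behind:
- First: 1/2. Second: 2/3.
- Third: 1/3 × 1 + 2/3 × 1/2 = 2/3.
- Fourth: 1.
- Mean = (0.500 + 0.667 + 0.667 + 1) / 4 = 70.8%, against 50% if nothing can be predicted.

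**Alternatives.** Fixed sizes were enumerated. Varying sizes were simulated for 150 patients, with an observer who knows the set of sizes but not their order and updates after each allocation.

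| Scheme | Certain | Best guess correct |
|---|---|---|
| Fixed 4 (as planned) | 33.3% | 70.8% |
| Fixed 6 | 25.0% | 68.3% |
| Fixed 8 | 20.0% | 66.6% |
| Varying 4/6 | 5.5% | 69.2% |
| Varying 4/6/8 | 2.3% | 68.0% |

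Varying 4/6/8 removes almost all the certainty but only 70.8 − 68.0 = 2.8 of the 20.8 points above chance, about 13%.

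**The case against.** A reader might infer that the recruiting team does know a third of allocations in advance and that the claimed concealment therefore fails. The documents do not support that, for these reasons:

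- The sequence is computer-generated, sits in REDCap and is released only after consent. Prediction needs knowledge of the block size and an exact ordered count across both arms. Nothing says that recruiters keep one.
- The person best placed to keep the count is the therapist who also coordinates. The article has the principal investigator and an unidentified team member recruiting, and does not say that this member is the therapist.
- Stratification, which would make counting harder, is not mentioned. In a condensed article, silence does not prove its absence.
- Candidates come from scheduled consultation lists, the principal investigator is to inform every eligible new patient, and Table 4 records eligible patients against participants. These steps limit or expose selective approach.
- The blinding phrase closes a sentence about allocation before the exercise programme begins, while the open-label statement concerns what follows. It is better read as the wrong word for concealment than as a direct contradiction.
- The calculation measures predictability. It gives no bias in QLQ-C30 points to set against the 10-point target.

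All of this stands, and it limits the point to what could happen. It does not remove the point. The fixed size is stated and published, nothing described prevents counting, and discretion over motivation and capability remains. The modest fall in the best-guess rate also stands: varying the block sizes is not enough by itself.

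**Conclusion.** The point holds in conditional form. As written, the scheme could allow a team member who keeps count to deduce about one third of allocations (about 49 of 150) and to guess about 71% correctly. Concealment fails for that predictable third and is weakened for the rest. It is not absent.

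This rests on 1:1 allocation, one unstratified list, and an observer who knows the block size and the full order of past allocations. The first is inferred from the equal group sizes, the second from the article's silence on strata; the third is possible but not shown. No claim is made that selective entry has occurred or that the effect estimate is biased by any given amount. Sample size, endpoint and analysis model are unaffected. The blinding phrase needs correcting in any case.

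**What to change.** 1. For patients still to be randomised, have the statistician load a new REDCap list with randomly varying block sizes, for example 4, 6 and 8. The statistician should hold the sizes, and they should not be disclosed to recruiting staff.
2. Make the switch at a block boundary. With a single list, this is when the number already randomised is a multiple of 4.
3. As far as existing roles allow, keep the running tally of allocations from those who approach and screen patients. This matters because varying sizes alone leave the best-guess rate at about 68%.
4. In Allocation and randomization, replace "ensuring blinding of the research team" with *concealed until assignment*.

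**Cost.** One new list and one changed phrase. With a largest block of 8, an unfinished last block can leave the arms up to 4 patients apart. A switch in the middle of an old block of 4 could add up to 2, making 6. The article does not say how many patients remain, so the gain from a new list cannot be sized.

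If recruitment has closed, only the wording can be corrected, and the predictability should be reported as a limitation.

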### Interventions

#### Usual supportive care

Both groups will receive the current standard of supportive care including whenever required guidance by a dietician on oral food intake, smoking cessation counseling, and speech and language therapist guidance concerning swallowing exercises, follow-up by the social workers, psychologists, and nurse care team. Additionally, they will be informed at the start of treatment about the importance of physical activities, and a brochure with general advice for exercises will be provided.

#### Dedicated comprehensive supervised exercise program (CSEP)

The intervention group will receive the CSEP, additional to usual supportive care. The CSEP consists of a one-hour individualized exercise program three times a week, starting within 1 week after the start of the CRT, taking into account motivation, personal goals, and pre-diagnostic activity level. The program is tailored to the acute effects of CRT as well (e.g., intensity and number of sessions). The training sessions will be organized in small groups of 3–4 patients, consisting of a combination of 30 min aerobic training at moderate intensity (walking, cycling) and 30 min resistance strength training and stretching (exercises for all major muscle groups and in particular the upper limb, head and neck region). A total of 18 supervised sessions are held in the hospital twice a week in week 1 to 6 and once a week in week 7 to 12, while the remaining one or two weekly sessions are performed independently at home. During the maintenance program (from week 13), patients will exercise at home with a monthly tele-consultation. Patients will have online access to videos of exercises to be performed at home. A selection of exercises will be made for each individual patient based on preferences and tailored to their exercise tolerance. During the tele-consultation, the physiotherapist discusses the progression of the training program at home and if any adjustments are needed.

The CSEP is supervised by a physiotherapist, [name]. The therapist will be dedicated full time to this program to conduct the patient assessments, to supervise the exercise sessions at the hospital and the tele-consultations during the maintenance program, and to coordinate the project. In addition to the exercise program, the participants in the intervention group attend in the first month an educational session about exercise during and after cancer treatment.

### Outcomes

#### Effectiveness study

At 5 time-points, evaluation moments are organized, during which self-reported questionnaires and clinical assessments are performed. The evaluation moments take place at baseline (T0), at 6 weeks (T1), at 12 weeks (T2), at 6 months (T3), and at 12 months (T4). The assessments will be performed at the Department Physical Medicine at the University Hospitals Leuven. Most of the questionnaires are conducted at home, through a digital link to the Research Electronic Data Capture (REDCap). The evaluation moments take place in the hospital. In total, administering the questionnaires through REDCap takes 60 min. The clinical assessment takes 45 to 60 min. The primary outcome parameter is health-related QOL measured with the European Organisation for Research and Treatment of Cancer quality of life questionnaire (EORTC QLQ-C30) at 6 months post-diagnosis. A key-secondary outcome is the physical functioning subscale of the EORTC QLQ-C30. The secondary outcome measures are also shown in Tables 2 and  3. In addition, personal factors, including patient-related factors (age, social status, work status), and cancer (treatment)-related factors will be collected from the participant’s medical file.

**Table 2 Tab2:** Study outcome measures by assessment time-point: self-reported outcomes

Domain	Questionnaire	*T*_0_	*T*_1_	*T*_2_	*T*_3_	*T*_4_
**Quality of life**						
Health-related quality of life (primary outcome)	EORTC QLQ-C30 [18] The EORTC QLQ-C30 is developed to assess the quality of life of cancer patients. The raw scores will be transformed to scores from 0 to 100 with 0 a worse health-related quality of life.	X	X	X	X	X
Disease-specific health-related quality of life	EORTC QLQ-HN43 [19] The EORTC QLQ-HN43 is a revised version specifically designed for HNC patients and used to measure the specific HNC symptoms. The scores range from 0 to 100. In functional scales, high scores represent a high level of functioning, while in symptoms, they represent a high level of symptomatology.	X	X	X	X	X
**Physical function**						
Pain	Brief Pain Inventory short form (BPI) [20] The BPI evaluates the severity of pain and its impact on functioning. The scores range from 0 to 10 with 0 no pain and 10 the worst possible pain.	X	X	X	X	X
Physical function	PROMIS physical function short form (PROMIS-PF-SF) [21–23] The PROMIS-PF-SF questions a set of person-centered measures that assesses and monitors physical health. The scores range from 1 to 5 with 5 the worst physical function.	X	X	X	X	X
Lymphedema	Lymphedema Symptom Intensity and Distress Survey—Truncal and Head and Neck (LSIDS-H&N) [24] The LSIDS-H&N rates the intensity and distress of 31 symptoms related to HNC (treatment). The scores range from 1 to 5 with 1 slight and 5 severe.	X	X	X	X	X
Fatigue	Functional Assessment of Chronic Illness Therapy—fatigue scale (FACIT-F) [25] The FACIT-F assesses an individual’s level of fatigue and its impact on daily activities and functions. The FACIT-F is scored on a 5-point Likert scale, where some items are reverse scored.	X	X	X	X	X
**Mental function**						
Depression, Anxiety and Stress	Depression, Anxiety and Stress Scale-21 (DASS-21) [26] The DASS-21 is a self-reported questionnaire that measures the three related states of depression, anxiety and stress. The DASS-21 is scored on a 4-point Likert scale, where scores for depression, anxiety, and stress are calculated by summing the scores for the relevant items.	X	X	X	X	X
Self-efficacy	General Self-Efficacy Scale (GSES) [27] The GSES measures how a person generally copes with stressors/difficult situations in life. The scores range from 1 to 4, with a higher score representing a better self-efficacy.	X	X	X	X	X
Stage of readiness to change	Patient-Centered Assessment and Counseling for Exercise (PACE) [28] The PACE determines your current physical activity level. The score ranges from 1 to 11 with 11 representing the most physical active level. The PACE intends to identify the stages of change for physical activity behavior.	X				
**Activity level**						
Physical activity level	International Physical Activity Questionnaire (IPAQ) [29] The IPAQ is a self-reported measure of physical activity. MET minutes a week are calculated to obtain 3 physical activity categories (high, moderate and low) with predefined criteria	X	X	X	X	X
Upper limb function	Short version of the Disability of Arm, Shoulder and Hand (QuickDASH) [30] The QuickDASH is a short self-reported questionnaire on upper limb function. The scores range from 1 to 5 with 5 impossible to perform the activity (and the 2 items “pain” and “pins and needles” with 5 extremely present).	X	X	X	X	X
**Participation**						
Return to work	Self-set questions about return to work, the current work situation, and information about job content	X	X	X	X	X
Social participation	Impact on Participation and Autonomy questionnaire (IPA) [31] The IPA contains questions about activities of daily life, with respect to autonomy and participation. The IPA is scored on a 5-point Likert scale with 0 very good and 5 bad regarding the possibility to perform some specific activities.	X	X	X	X	X
**Exercise**						
Safety	Physical Activity Readiness Questionnaire (PAR-Q) [32] The PAR-Q is designed to help uncover any potential health risks associated with exercise. It is a self-screening tool to determine the safety or possible risks of exercising based on health history, symptoms and risk factors. Yes or no can be answered.	X				
Motivation towards exercise	Behavioral Regulation in Exercise Questionnaire 2 (BREQ-2) [33] The BREQ-2 evaluates behavioral regulation in exercise, in particular motivation to exercise. The BREQ-2 is scored on a 5 point Likert scale (0 = not true for me, 4 = very true for me)	X		X		X
Satisfaction with the supervised intervention at the hospital (IG^a^)	Self-composed set of questions on a 5-point scale about the feasibility (practical, mental, physical), the intensity, the motivation during and the results of the exercise program in the hospital, and the competence of the physiotherapist.			X		
Satisfaction with the intervention at home (IG^a^)	Self-composed set of questions on a 5-point scale about the feasibility (practical, mental, physical), the intensity, the motivation, and the results of the exercise program at home and the added value of the teleconsultations with the physiotherapist.				X	

*T*_0_ = baseline, *T*_1_ = 6 weeks, *T*_2_ = 12 weeks, *T*_3_ = 6 months, *T*_4_ = 12 months

^a^IG = intervention group

**Table 3 Tab3:** Study outcome measures by assessment time-point: clinical assessments

Domain	Clinical assessment	*T*_0_	*T*_1_	*T*_2_	*T*_3_	*T*_4_
**Physical function**						
Body composition	Bio-impedance Spectroscopy with the InBody device [34, 35] measuring the body composition, with as most important outcome parameters: body mass index (BMI), extracellular water (ECW) ratio, fat free mass, phase angle, and the skeletal muscle index (SMI) to determine sarcopenia.	X	X	X	X	X
External lymphedema	A tissue dielectric constant measurement to determine the %water content at different local points, with the device MoistureMeterD Compact of Delfin [36, 37]. 6 points bilateral in the head and neck area (and 1 point submental) are measured according to the protocol “Lymphscanner/MoistureMeter head and neck area” of C.R. [38] of the Netherlands Cancer Institute (2021).	X	X	X	X	X
External lymphedema	Neck circumference tape measurements at the 3 points in the neck area of the previous protocol [39].	X	X	X	X	X
Fibrosis	Common Toxicity Criteria (CTC) Version 3.0 [40] The CTC grades the severity of possible fibrosis in the acute phase.	X	X	X		
Fibrosis	EORTC/RTOG 5-point scale [41] The EORTC/RTOG grades the severity of possible fibrosis in the more chronic phase.				X	X
Upper limb strength	Jamar Handheld dynamometer [42] This handheld dynamometer measures the handgrip strength.	X	X	X	X	X
Shoulder range of motion	Inclinometer [name]: anteflexion, abduction [43] The active range of motion in the shoulder, anteflexion and abduction, are measured with the inclinometer.	X	X	X	X	X
Physical fitness	6-min walking distance [44] The 6-min walk test assesses aerobic capacity and endurance, giving information about the functional capacity.	X	X	X	X	X
Lower limb strength	Leg press 1 repetition maximum (1RM) The 1RM of the quadriceps is determined during the leg press test, which assesses the maximum muscular strength of the quadriceps.	X	X	X	X	X
**Activity level**						
Physical activity	One ActiGraph wGTX3X-BT accelerometer on the right waist (7 consecutive days) will be worn during waking hours [45], during 7 consecutive days. During sleep, the accelerometer will be worn on the right wrist [46, 47]. Outcome parameters are activity kcals, steps, METs, sedentary time, light vigorous time, moderate vigorous time, vigorous time, and very vigorous time.	X	X	X	X	X

*T*_0_ = baseline, *T*_1_ = 6 weeks, *T*_2_ = 12 weeks, *T*_3_ = 6 months, *T*_4_ = 12 months

#### Feasibility study

The feasibility study exists of a quantitative and qualitative part. First, the quantitative feasibility outcome measures are collected in all participants of the clinical trial, at baseline (T0), 12 weeks (T2), and/or 6 months (T3) follow-up. The outcomes of interest are displayed in Table 4. Second, the qualitative part of the feasibility study consists of organizing focus groups. For the focus group, we anticipate to engage 15 participants out of the total group of 150 participants at each time point (baseline, 12 weeks, 6 months). Review of the literature indicates that data regarding feasibility is typically achieved within 2 to 3 cycles of focus groups [48]. Additionally, data saturation can usually be reached with samples as small as 5 to 7 participants per group. Therefore, we aim to recruit 15 consumers for 2 to 3 focus groups. The aim of these focus groups is to capture qualitative data regarding barriers and facilitators for participating in the CSEP that provided explanation and additional information to the quantitative questionnaire. The focus group leader will ask a series of open-ended questions based predefined subjects. Another researcher will observe the focus groups. All focus group sessions will be video recorded and transcribed.

**Table 4 Tab4:** Feasibility outcomes: quantitative part

Quantitative outcomes	Explanation	*T*_0_	*T*_1_	*T*_2_	*T*_3_	*T*_4_
Acceptance of the invitation to participate	Eligible patients vs participants	x				
Compliance and adherence to the intervention schedule	For example, adherence to CSEP program, intervention attendance and engagement in scheduled sessions, prescribed frequency, intensity, time, and type of exercise (collected using a diary)			x	x	
Sample characteristics	Sample characteristics based on education level, age, self-efficacy, type of cancer to identify subgroups of head and neck patients who participate, adhere best to the program and would benefit the most of it	x		x	x	
Retention of participants	It is estimated by 6-month follow-up rates				x	

*T*_0_ = baseline, *T*_1_ = 6 weeks, *T*_2_ = 12 weeks, *T*_3_ = 6 months, *T*_4_ = 12 months

